### Statistical methods and analysis

#### Analysis of equivalence of two arms at baseline

The equivalence will be analyzed by using *Mann-Whitley U* test, *Chi-square* test, *t* test or *ANOVA*.

#### Analysis of intervention outcomes

For intervention arm and control arm comparison, indicators of rates of HIV/STDs infection, consistent condom use, adherence to regularly HIV testing and sexual risk behaviors at baseline and at 6-, 12- and 18-month will be compared by using Chi-square test. And a COX risk model will be used for predicting HIV/STDs infection risks.

For the cost-effectiveness analysis, the total cost consists of direct and indirect cost mentioned above. Effectiveness covers the increased rates of consistent condom use and regularly HIV testing, the decreased rate of HIV/STDs infection, relative risk of HIV/STDs infection. A decision analytic model will be used to evaluate economic evaluation of the intervention. Using the estimated effectiveness and incremental cost of per HIV infection case decreased, every 1% decrease of HIV/STDs infection, every 10% increase of consistent condom use or adherence to regularly HIV testing, incremental cost-effectiveness ratio will be calculated.

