#### Data collection

Baseline data of all the subjects will be collected at the enrollment procedure. The measures including demographic information (*age, marital status, current occupation, educational level, income and sexual orientation*), sexual behaviors (*number of male and female sex partners, frequency of sex, sex role, commercial sex behaviors, sex with fixed and casual sexual partners*), and health-related behaviors (*consistent condom use with multi-type of sex partners, regular HIV testing, drug use experience and sexual transmitted diseases infection history*).

For the rest three times of data collection, sexual behaviors, health-related behaviors, and app user experience (*user experience, feedback and suggestions*) during the last 6 months will be involved in an electronic questionnaire. One version will be made into the app and be delivered every 6 months to intervention arm participants. Another without app user experience items will be delivered by Wechat to the ones in control arm.

Data of cost of the intervention and participants’ app use behaviors will also be collected. Direct cost involves cost of development, operation and maintenance of this app and worker cost, indirect cost consists of participants’ expenses due to their joining in the study such as time spending, cell phone internet data and traffic cost. App use behaviors will be collected through the management system which involves participants’ use frequency and time durance, information scanned, interaction times and frequency.

We use the electronic questionnaire to make sure that all of the items will be presented in a logical order and necessary answers missing will not be allowed. The participant will be offered a non-cash financial compensation as phone bills worth 20 RMB for compensation every time he complete the data collection.

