#### Sample size and calculation

The intervention arm and control arm are of equal size and two-tailed hypothesis testing is assumed. Sample size is calculated by using the specific sample size function module PASS on the statistical analysis software NCSS [42]. By setting the α = 0.05, 1-β = 0.9, effect size as 0.25 [43], the sample size of each group is 336. With an estimated 20% loss to follow-up, 400 subjects are necessary for each group.

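### Chi-square is the only between-arm test named for sexual risk behaviours, so partner number and frequency of sex can be compared as planned only after being cut into categories

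*Protocol article*

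**What the plan says.** The Data collection section of the protocol article lists the baseline sexual-behaviour items as "number of male and female sex partners, frequency of sex, sex role, commercial sex behaviors, sex with fixed and casual sexual partners". The first two are counts or frequencies; the others are largely categorical. Sexual behaviours are asked about again at each of the three follow-ups, with a six-month recall.

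Analysis of intervention outcomes gives one method for comparing the arms. It names indicators of rates of infection and consistent condom use, and then "adherence to regularly HIV testing and sexual risk behaviors at baseline and at 6-, 12- and 18-month will be compared by using Chi-square test". The only other between-arm model in that section is a Cox model, for HIV/STD infection. Rank tests, t tests and ANOVA are named once, in the section on baseline equivalence.

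The abstract counts sexual risk behaviour among the effectiveness measures. The Outcome measures section lists it neither as primary (infection rates and relative risk) nor as secondary (condom use and testing adherence).

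The sample-size section says that "two-tailed hypothesis testing is assumed" and continues: "By setting the α = 0.05, 1-β = 0.9, effect size as 0.25 [43], the sample size of each group is 336". The type of effect size is not stated.

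**The concern.** A Chi-square test compares proportions across categories, so a count has to be grouped before it can be used. Once grouped, only movement across a boundary is seen. With a cut at two partners, a man who goes from ten partners to four counts as unchanged. An intervention that lowers partner number or frequency of sex could then go undetected, although the trial holds the data to show it. How much is detected also depends on where the cut falls.

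This is a point about a method the article states, not about detail left to another document: an analysis plan that follows the sentence would have to categorise these two measures. It is about the scale of analysis only, not about baseline adjustment or repeated visits.

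**Working it through.** **Inputs from the article (Sample size and calculation).** Two-sided α = 0.05, power 0.90, effect size 0.25, 336 per arm, 20% loss, 400 per arm enrolled. Completers: 400 × 0.8 = 320 per arm.

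**Step 1: reproduce the plan's figure.** Reading 0.25 as a standardised mean difference d:

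n = 2 × (1.960 + 1.282)² / 0.25² = 336.2 per arm.

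This matches 336. Reading 0.25 as Cohen's h for two proportions gives the same number (50% vs 37.6%, for example, needs 336 per arm). The figure therefore cannot tell us which was meant. Step 2 assumes d.

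**Step 2: normal scale, d = 0.25 (assumption).**

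- Uncut: power = Φ(0.25 × √(n/2) − 1.96). At n = 336 this is Φ(3.240 − 1.96) = 0.900.
- Median split: the proportions above the pooled median are Φ(0.125) = 0.550 and Φ(−0.125) = 0.450. Power = Φ{[0.0995 × √n − 1.96 × √(2 × 0.5 × 0.5)] / √(2 × 0.550 × 0.450)}. At n = 336 this is Φ{(1.824 − 1.386) / 0.704} = Φ(0.622) = 0.733.

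| n per arm | Uncut | Median split | Loss (points) | Loss, 70:30 cut | Loss, 80:20 cut |
|---|---|---|---|---|---|
| 320 | 0.885 | 0.712 | 17.3 | 21.8 | 29.0 |
| 336 | 0.900 | 0.733 | 16.7 | 21.2 | 28.4 |
| 400 | 0.942 | 0.805 | 13.8 | 18.0 | 25.1 |

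More categories do not recover the loss with an ordinary Chi-square test: at 320 per arm, three to six equal groups give power of 0.710 falling to 0.629.

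**Step 3: skewed counts (all inputs assumed).** Negative binomial with variance = mean + mean²/k, 336 per arm, 4,000 simulated trials per row. The article gives no mean, dispersion or rate ratio for these measures.

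| Control mean, k, rate ratio | Rate-ratio test | Mann-Whitney | Chi-square, 2 or more | Chi-square, 5 or more |
|---|---|---|---|---|
| 4, 1, 0.75 | 0.90 | 0.81 | 0.55 | 0.75 |
| 3, 1, 0.75 | 0.89 | 0.78 | 0.57 | 0.73 |
| 4, 0.7, 0.75 | 0.81 | 0.65 | 0.42 | 0.61 |
| 3, 2, 0.80 | 0.87 | 0.80 | 0.56 | 0.70 |

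Against the rate-ratio test, the cut at five loses 15, 16, 20 and 17 points, and the cut at two loses 35, 32, 39 and 31. Trying every low cut at 320 to 336 per arm, even the best one, which cannot be known beforehand, loses roughly 13 to 19 points. Against Mann-Whitney the cut at five loses 6, 5, 4 and 10 points, and the best cut about 2 to 12.

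**Step 4: a case where the loss nearly vanishes.** With mean 3, k = 0.5, a standardised difference of 0.25 and 320 per arm, power is 0.895 for a t test, 0.753 for Mann-Whitney and 0.751 for the best of the cuts tried (one, two, three or five). The loss is 14 points against a mean-based test and about zero against the rank test.

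**The case against.** The strongest reply is that the article never says partner number or frequency of sex is itself a tested outcome. The sentence is about rates, and the sexual risk behaviour indicator is not defined. Several collected items are naturally categorical, and the app's own behavioural assessment module looks at unprotected sex and condom use. If the indicator is a yes/no item such as any commercial sex, Chi-square fits and nothing is lost. That stands, and it confines the point to the two measures collected as counts or frequencies.

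The outcome's standing is also modest. A reader might infer that a primary analysis is under-powered. The article does not support this: sexual risk behaviour is in neither outcome list, and the sample-size section does not say which outcome it serves.

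A reader might further take 17 points as a minimum loss. It is not. It rests on reading 0.25 as d on the count scale, whereas h reproduces 336 equally well, and on that reading Chi-square has about the planned power for the proportions it was sized on. The loss is 13.8 points at 400 per arm and can be small against a rank test.

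Nor are the missing definition and cut-point errors here; a condensed article commonly leaves them to a fuller document. The generic list of baseline tests shows no inconsistency either, since age and income need such tests. What remains is that the one stated test does not suit two of the measures collected.

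**Conclusion.** The point holds in a limited form. As written, number of partners and frequency of sex can be compared between arms only after categorising, and this gives up information already collected. It concerns an effectiveness measure named in the abstract, and is worth changing because the change is cheap.

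The size is an illustration. For a standardised difference of 0.25 it is a fall from about 0.89-0.90 to 0.71-0.73 with 320 to 336 per arm and a median split, and about 14 points at 400. For over-dispersed counts with an assumed mean of 3 to 4 and rate ratio of 0.75 to 0.80, it is roughly 13 to 40 points against a rate-ratio test, running from the best cut to a cut at two or more, and less against Mann-Whitney. The direction is the same throughout; the amount depends on the distribution, the cut and the comparator, none of which the article fixes.

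**What to change.** In Analysis of intervention outcomes, keep Chi-square for outcomes that are binary: infection, consistent condom use, adherence to regular testing and yes/no risk items. Add one sentence for number of partners and frequency of sex: compare the arms on the original scale with a negative binomial model, reporting a rate ratio with robust standard errors, and use the Mann-Whitney test, already named for baseline, as a check against extreme values. A categorised version, such as multiple partners yes/no, may be reported alongside with its cut set in advance.

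The cost is that sentence and a little programming; no further data, participants or visits are needed. The small downside is that a rate ratio is less immediate to readers than a percentage and is sensitive to very large reported counts. The rank test and the accompanying percentages cover both.

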#### Participant follow-up

All of the subjects in control and intervention arms will attend four visits, one at baseline for screening and enrollment, three at 6-, 12-, 18-month respectively to assess their sexual and other health behaviors (detailed below). Any subject gets HIV infected during the whole study period will be referred to professionals for timely treatment and withdrawn form the study. Information and psychological counseling services, positive sex tips and necessary links to care resources will be provided by the study staff.

Figure 1 is the Participant flow chart of the study.

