#### Outcome measures

Outcomes will be compared between intervention and control arms, and between different time points of each arm. The primary outcomes include HIV/STDs infection rates, relative risk of HIV/STDs infection, secondary outcomes include condom use rates, adherence to regularly HIV testing. The incremental cost is defined as per HIV infection case decreased according to the app-based intervention, cost of every 1% decrease of HIV/STDs infection, or every 10% increase of consistent condom use and adherence to regularly HIV testing. Another outcome is the app-based intervention mechanism (detailed below).

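### Visit-by-visit unadjusted Chi-square tests of condom use, HIV testing and risk behaviour are valid, but discard precision that the collected baseline values would give

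*Protocol article*

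**What the plan says.** All references are to the Protocol article.

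- *Analysis of intervention outcomes*: for the comparison of the two arms, "indicators of rates of HIV/STDs infection, consistent condom use, adherence to regularly HIV testing and sexual risk behaviors" are listed, and these "at baseline and at 6-, 12- and 18-month will be compared by using Chi-square test". The only regression named for an effectiveness outcome concerns infection: "a COX risk model will be used for predicting HIV/STDs infection risks".
- *Data collection*: the baseline record includes "consistent condom use with multi-type of sex partners, regular HIV testing, drug use experience and sexual transmitted diseases infection history" and, for sexual behaviour, "number of male and female sex partners, frequency of sex, sex role, commercial sex behaviors, sex with fixed and casual sexual partners".
- *Participant follow-up*: after the baseline visit there are "three at 6-, 12-, 18-month respectively to assess their sexual and other health behaviors".
- *Outcome measures*: "Outcomes will be compared between intervention and control arms, and between different time points of each arm". No test is named for the second kind of comparison. Condom use and HIV testing adherence are secondary outcomes; infection is primary.
- *Analysis of equivalence of two arms at baseline*: "The equivalence will be analyzed by using" a list of significance tests.

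**The concern.** The plan does not leave the method open. It names a test for the behavioural outcomes, and that test takes no covariate and looks at one visit at a time. A man's past condom use or testing habit is likely to predict his later habit. Where it does, an analysis that conditions on the baseline value estimates the difference between arms with a smaller standard error from the same men. Under the stated plan this gain is lost.

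Two consequences follow from looking at visits one by one. The test statistic does not link a man's answers across visits, so it offers no basis for the announced comparisons over time. The stated use of baseline in comparing the arms is to test whether they differ there. In a randomised trial such a test answers no useful question: any difference is due to chance, and a non-significant result does not show equivalence.

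At stake is the width of the confidence intervals, and the power, for the behavioural results. Condom use and HIV testing also feed the cost-effectiveness ratios.

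**Working it through.** **Inputs from the documents** (*Sample size and calculation*): two-sided α = 0.05, power 0.90, effect size 0.25, 336 per group, 20% loss, 400 recruited per group.

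**Input not in the documents:** the correlation ρ between baseline and follow-up values of the same behaviour. I take 0.2 to 0.6 as an assumed range.

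**Step 1. Reproduce the plan's figure.** For two groups compared once, without adjustment, on a standardised difference of 0.25:

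n = 2 × ((1.960 + 1.282) / 0.25)² = 336.2 per group.

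This matches the stated 336 (337 if rounded up). The same formula applies if 0.25 is Cohen's h for two proportions. The planned size therefore takes no credit for baseline or repeated measurement, in line with the Chi-square plan.

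**Step 2. Gain from baseline adjustment at one visit.** For a difference in means or risks, adjusting for baseline multiplies the variance by 1 − ρ². The equivalent increase in sample is 1/(1 − ρ²), and the n giving the same power is 336 × (1 − ρ²), rounded up. Power with 320 men per arm (400 × 0.8) is Φ(0.25 × √(320/2) / √(1 − ρ²) − 1.960).

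| ρ (assumed) | Variance cut | Sample multiplier | n in place of 336 | Power at 320 per arm |
|---|---|---|---|---|
| none used | 0% | 1.00 | 336 | 88.5% |
| 0.2 | 4% | 1.04 | 323 | 89.8% |
| 0.3 | 9% | 1.10 | 306 | 91.2% |
| 0.5 | 25% | 1.33 | 252 | 95.5% |
| 0.6 | 36% | 1.56 | 216 | 97.7% |

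The power column is illustrative. The protocol does not say which outcome the effect size of 0.25 refers to.

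**Step 3. Check with binary data.** Correlated yes/no outcomes were simulated with 320 men per arm and 4,000 runs per scenario. Risks at 18 months were 0.50 and 0.624 (h = 0.25). The Chi-square test was set against a risk-difference regression on arm and baseline.

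| Binary correlation, about | Power, Chi-square | Power, adjusted | Variance ratio, simulated | 1 − ρ² |
|---|---|---|---|---|
| 0.3 | 88% | 91% | 0.91 | 0.91 |
| 0.5 | 88% | 95% | 0.78 | 0.75 |
| 0.7 | 89% | 99% | 0.54 | 0.51 |

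With no true effect, both methods rejected in 4.5% to 6.0% of runs, close to the nominal 5%. So the formula holds well for a binary outcome, slightly overstating the gain at higher correlations, and the Chi-square test is not invalid.

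**Step 4. What the repeated visits add.** With complete data and an arm-by-visit term, precision for the 18-month effect comes mainly from the baseline value. The other visits would add much more only if the target were the average effect over three visits: at ρ = 0.5 its variance factor is (1 + 2 × 0.5)/3 − 0.5² = 0.42. That presumes a constant effect and is a different question, so it is not claimed here.

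**The case against.** The strongest reply is that this is preference, not error. At any one visit the two arms contain different men, so an unadjusted Chi-square test under 1:1 randomisation is sound. That stands, and it limits the point to efficiency. It is also fair that the correlation is unknown and that a low value leaves little to gain: 4% at 0.2. Nor does the recommendation reach the primary outcomes.

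The reply does not remove the point. The test is stated, the baseline values are collected, and the better analysis is nearly free.

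A reader might infer more than the text supports:

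- **That the within-arm comparisons use the wrong variance.** *Outcome measures* announces them, but no section assigns Chi-square or any other test to them. A paired method is not excluded.
- **That chance baseline imbalance biases the result.** Under randomisation it is random error that the unadjusted test already counts. It is the precision point again.
- **That no effect size will be available.** The cost-effectiveness text works with increases in rates of condom use and testing, so rate differences are implied. Naming a test does not rule out reporting estimates.
- **That the baseline infection comparison is empty.** This is so for HIV only, since men must be HIV negative to enter. STDs can differ at baseline. The HIV part is harmless.
- **That baseline behaviour is used nowhere else.** The imputation, attrition propensity and Cox models do not list their predictors, so this can be neither asserted nor denied.

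**Conclusion.** The point holds as one of efficiency for the behavioural outcomes. The stated visit-wise Chi-square tests are valid but discard precision that the trial already pays to collect. For a risk difference, the avoidable variance is about 4% to 36% if ρ is 0.2 to 0.6, equivalent to about 4% to 56% more men. The range is an assumption, and the documents cannot narrow it. They leave the baseline recall period unstated, while follow-up items cover six months; the baseline value can still serve as a covariate.

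The gain applies to a marginal risk difference. It does not carry over to a covariate-adjusted odds ratio, because adjustment in a logistic model changes the quantity estimated and its standard error need not shrink. The effect measure therefore has to be named together with the model. The documents do not support a claim of bias or inflated type I error in the between-arm tests.

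**What to change.** In *Analysis of intervention outcomes*, replace the visit-wise Chi-square tests for the behavioural outcomes as follows.

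1. For each such outcome, fit one logistic model to the 6-, 12- and 18-month data, by GEE or with random effects, containing arm, visit, arm-by-visit and the baseline value of that outcome.
2. Report as the effect the 18-month risk difference between arms with its 95% CI, standardised over the baseline distribution of all randomised men. Do not use the adjusted odds ratio. If random effects are used, average the predicted risks over them, so that the difference is marginal.
3. Take the changes over time announced in *Outcome measures* from the same model, so that correlation within a man is respected. State that change within one arm is not evidence of an app effect.
4. Replace the baseline significance tests with a descriptive table by arm.

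The cost is a revised paragraph, a little more programming and reliance on a working model. No data, visits or participants are added, and the primary HIV/STD infection analysis stays as it is.

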The objectives of the study are to (1) design and develop an easy to use, user-friendly, non-stigmatized and free app, and deliver app-based HIV prevention intervention to MSM, and (2) to evaluate the effectiveness of the app at decreasing rate of HIV infection, promoting HIV testing behavior and consistent condom use among MSM, and cost-effectiveness analysis of the intervention. App-based intervention mechanism will also be explored.

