## Participants

### Inclusion and exclusion criteria

Participant inclusion criteria: (1) male aged 16 years or older, (2) has experience of same-sex anal intercourse during the last 12 months, (3) HIV negative, (4) own at least one smartphone, and (5) willing to report individual HIV/STDs testing results to the researcher. Participant exclusion criteria:(1) has only one sex partner who is also HIV negative, and their relationship has last for more than 2 years, (2) unable to participant the program because of cognitive or psychiatric disorders, or (3) has already attended another intervention program.

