### Recruitment

For the participant enrollment, in phase 1 and phase 2, MSM who are potential eligible for the study will be listed, and each individual will be invited to take free HIV testing and participate in the study through phone call performed by the staff of CDC and the two NGOs. An appointment will be made if the person agrees to participate. Following an oral informed consent, clients will be screened for eligibility as subjects of the study by a research member, demographic information and baseline data(details below) will be obtained, and blood samples will be taken for HIV testing. Written informed consent will be obtained from each one who is HIV-seronegtive and willing to participate in the study. Those HIV-seropositive persons will be referred to local CDC for verification and treatment.

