## Procedures

### Phase 1: Development of the app

First, on the basis of our previous studies and references reviewing, preliminary functional modules of the app were presented in Table 1 below. Next step of this study is to search and evaluate currently exist domestic HIV/STDs prevention and treatment related apps on Apple.

**Table 1 Tab1:** Function modules of HIV prevention app for MSM

Name	Function description
Behavioral assessment	Assessment about user’s unprotected sex behaviors and condom use rate
Behavior change plans	Setting personal goals and plans of health behavior change, and individualized reward/punishment plans
Counseling	Buttons for enter into phone, message, Wechat and email counseling areas
Health education	Knowledge about HIV diagnosis, prevention and treatment, skills of condom using, etc
Personal health records	Uploading HIV/STDs testing results, building personal health records and health promotion plans
Information push	Delivering latest news HIV prevention, treatment and related policies, and reminders of personal behavior, encouragement and advice
Experts encouragements	Videos from professionals and celebrities to encourage user’s adherence to behavior change efforts
Institutions introduction	Providing information about addresses, connection methods, providers and services offered of CDC, hospitals, NGOs nearby
Feedback platform	Building a communication platform where users can give feedback of using the app
Setting	Settings of time period of receiving information, passports of log in the app, latest versions, etc

Store and Android Market since the two markets occupy 90.61% of the current mobile application markets [41]. We use the words “HIV/AIDS/human immunodeficiency virus/STD/ sexually transmitted disease/sexual health/sexual behavior/positive sex/condom” respectively to search for related apps, each eligible app will be downloaded and its features, including names, download numbers, target population, main function modules will be listed and analyzed.

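### No common follow-up HIV/STD test is stated and the app aims to raise testing, so both the chi-square and Cox comparisons of infection can mix testing uptake with infection

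*Protocol article*

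**What the plan says.** **Outcome and analysis.** Under Outcome measures, "The primary outcomes include HIV/STDs infection rates, relative risk of HIV/STDs infection". Under Analysis of intervention outcomes, the arms are compared by chi-square at baseline and at 6, 12 and 18 months, and "And a COX risk model will be used for predicting HIV/STDs infection risks". Event time and censoring are not defined there.

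**How infection becomes known.** At enrolment, "blood samples will be taken for HIV testing" (Recruitment). After that:
- the three follow-up visits are described as held "to assess their sexual and other health behaviors" (Participant follow-up);
- follow-up data come by electronic questionnaire, inside the app for one arm and by Wechat for the other (Data collection);
- an inclusion criterion is that the man is "willing to report individual HIV/STDs testing results to the researcher";
- one app module is "Uploading HIV/STDs testing results, building personal health records and health promotion plans" (Table 1), and the Control group section describes no counterpart.

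**Testing as a target.** The objectives include "promoting HIV testing behavior and consistent condom use among MSM", and "secondary outcomes include condom use rates, adherence to regularly HIV testing". Study design lists voluntary counseling and testing among the usual-care services.

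**Missing endpoints.** The Intention-to-treat section imputes them by EM and repeats the analysis with multiple imputation. It does not say whether a man with no test result counts as missing or as uninfected.

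**The concern.** An infection is known only to lie between a man's last negative and first positive test. When both arms are tested at the same times, this coarseness is nearly harmless. When men choose when to test, and one arm is encouraged to test more, the arm that tests more finds a larger share of its infections and finds them sooner.

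The plan sets out to change the process by which its primary event is observed, and the text makes no allowance for this. The chi-square comparison and the Cox model are both exposed, because the cause is unequal ascertainment and not the choice of Cox. The bias runs against the app and grows with the app's success on its own secondary outcome. It also carries into the cost per infection averted, which uses the same contrast. The limitations in the Discussion mention bias from the open design but not detection bias.

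**Working it through.** **What can be reproduced.** The plan gives no incidence or testing figure. Its one calculated figure, 336 per group, follows from 2 × ((1.960 + 1.282)/0.25)² = 336.2 but does not bear on this point. Everything below rests on assumed incidence and testing shares.

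**Step 1: expected detections, low incidence, no true effect.** Assume test opportunities at 6, 12 and 18 months, each used with probability p, independently of infection. Infections arise equally in the three periods. The probability of detection by month 18 is 1 − (1 − p)³, 1 − (1 − p)² and p for infections in periods 1, 2 and 3. Summing, out of a possible 3:

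| p | Period 1 | Period 2 | Period 3 | Sum |
|---|---|---|---|---|
| 0.8 | 0.992 | 0.960 | 0.800 | 2.752 |
| 0.5 | 0.875 | 0.750 | 0.500 | 2.125 |
| 0.9 | 0.999 | 0.990 | 0.900 | 2.889 |
| 0.7 | 0.973 | 0.910 | 0.700 | 2.583 |

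Apparent risk ratio, app to control: 2.752/2.125 = 1.30 for 80% versus 50%, and 2.889/2.583 = 1.12 for 90% versus 70%. The true ratio is 1.

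**Step 2: Cox estimate.** The same testing model was used with incidence of 5 or 15 per 100 person-years, the event placed at the detecting test, men without a positive test censored at month 18, and Breslow ties. The estimate was solved from expected counts.

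| Testing per 6 months, app vs control | True HR | Cox HR | Detected-risk ratio |
|---|---|---|---|
| 80% vs 50% | 1.0 | 1.30–1.31 | 1.29 |
| 90% vs 70% | 1.0 | 1.12–1.13 | 1.11–1.12 |
| 80% vs 50% | 0.7 | 0.91–0.93 | 0.91–0.93 |
| 90% vs 70% | 0.7 | 0.79–0.80 | 0.79–0.80 |

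The detected-risk ratio, which underlies the chi-square test, moves almost as far as the Cox estimate.

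**Step 3: wider testing gaps.** A separate simulation let testing occur at any time, with 1,000,000 men per arm and 3 to 8 infections per 100 person-years. With a true HR of 1.0, the Cox HR was 1.26–1.28 for 70% (app) versus 50% (control), 1.49–1.52 for 50% versus 30%, and 1.89–1.92 for 70% versus 30%. With a true HR of 0.7 the same pairs gave 0.89–0.90, 1.05–1.06 and 1.33–1.35.

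**Step 4: common testing.** If all men are tested at 6, 12 and 18 months (5 per 100 person-years), the Cox HR is about 1.00 for a true 1.0 and about 0.71 for a true 0.7. If testing is as in Step 2 but every man is also tested at month 18, a true 1.0 appears as 1.01–1.03 and a true 0.7 as 0.71–0.72.

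**Step 5: interval-censored model.** In 200 simulated datasets of 8,000 men per Step 2 scenario with true HR 1.0, a piecewise-constant interval-censored model returned 1.00 to 1.01. Testing in that simulation was unrelated to infection within arm.

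**The case against.** **The Cox specification is inferred.** A reader might infer that the plan states an event time at detection, with everyone else censored at month 18. It does not, and a condensed article may leave such rules to the full protocol or SAP. That stands. What remains is that infection can be observed only through a test result, and the article describes results as ones men report.

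**Common testing is not excluded.** Infection rates are to be compared at 6, 12 and 18 months, both arms attend the same visits, the partner CDC verifies HIV status, and the flow chart is not shown. A reader might infer that the trial does no follow-up testing; the text does not establish that. Equally, a common visit schedule is not a common test schedule, and access to voluntary testing does not make testing equal between arms.

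**Imputation might change the picture.** If untested men are treated as missing, the analysis is not the one modelled above. The article does not say, so the treatment of these men needs to be stated.

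**The bias is small beside the noise.** At 5 per 100 person-years, 800 men yield about 800 × (1 − exp(−0.075)) = 58 infections, so the standard error of log HR is at least 2/√58 = 0.26. A bias of log 1.31 = 0.27 is about one standard error, and log 1.13 = 0.12 is under half. This is fair, but the bias is systematic and comes on top of limited precision.

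**The remedy has its own assumption.** If men test because of symptoms or recent risk, test times are informative and an interval-censored model can be biased too. This stands, and favors a common test where one is possible.

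**Conclusion.** The point holds as a problem of unequal ascertainment affecting both the chi-square and the Cox analysis. On the text shown, nothing secures equal testing in the two arms, and the intervention is meant to make testing unequal. If testing rises in the app arm, a true HR of 1.0 appears as about 1.3 (80% versus 50%) or 1.1 (90% versus 70%), and a true benefit of 0.7 is diluted to about 0.9 or 0.8.

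The size rests wholly on assumed testing shares and incidence, on an inferred event time, and on untested men being counted as uninfected. With common testing at the visits, or one test for all at month 18, almost nothing is left.

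Two stronger readings are not supported. The first is that the fault lies in the Cox model alone: the detected-risk ratio is distorted almost equally, so replacing Cox and leaving the chi-square test as it is would not cure it. The second is that the trial would report the app as harmful: reversal of a real benefit needs a wide testing gap or low control testing, and at moderate gaps the benefit is diluted but keeps its direction.

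**What to change.** 1. **State the follow-up testing.** If the full protocol already tests both arms on a common schedule, say so and base the infection endpoint on those tests. That settles most of the point.
2. **Otherwise, record dates.** Collect each man's last-negative and first-positive test dates, separately for HIV and each STD, by the same method in both arms.
3. **Change the arm comparison.** Use an interval-censored proportional hazards model or a complementary log-log discrete-time model. Censor untested men at their last negative test and do not count them as uninfected. Report the arm hazard ratio with 95% CI.
4. **Limit the chi-square comparison.** At each visit, report it only among men with a test result, alongside testing shares by arm, and call it descriptive. After month 6 it is not free of the problem, because men found infected are withdrawn. Among men tested at month 12 and not found positive before, the expected positives are (1 − p) + 1 in units of one period's risk: 1.2 at p = 0.8 against 1.5 at p = 0.5, a ratio of 0.80 with no true effect.
5. **Reconcile with the Intention-to-treat section.** State how the EM and multiple imputation treat men without a test result.

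**Cost.** Revised wording and test dates. Men already agree to report results, but the article does not mention dates. The interval will be slightly wider, and the model assumes that test timing is unrelated to infection given arm, which should be stated.
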